#### **4.5 Intervention and implementation procedure**

Patients will be referred for CR from the medical team in the chest clinic; the referral shall be based on the inclusion and exclusion criteria. The referring of patients for screening and enrolment shall be terminated after the eight-week period. All patients will be screened again for CR eligibility using the set inclusion and exclusion criteria; following which a thorough assessment will be conducted for each patient (Appendix 10) . Briefly, the following parameters will be recorded for each patient; demographic data, medical and social history (including medications and dosages), resting Blood Pressure (BP), Pulse Rate (PR), Respiratory Rate (RR), Body Weight (BWT), Height (H), Body Mass Index (BMI) and exercise capacity.

Furthermore, risk stratification will be conducted to ascertain the risk for cardiac events during the exercise therapy; although the low-moderate risk category of patients will be offered close supervision to ensure safe exertion, all high risk patients will be excluded from exerting. In addition, each patient will be risk stratified for disease progression, to ascertain availability of risk factors and the risk for rapid progression of the disease; this will assist the therapists to plan and deliver an effective education and counselling intervention to influence life style modification. Thereafter, exercise tolerance test will be conducted using 6-minute walk test; this will assist therapists to prescribe the appropriate and safe target exertion zone at which each patient must exercise to gain positive results.

FITT (Frequency, Intensity, Time and Type) principle will be used to prescribe the exercise therapy. Table 1 describes the parameters which will be used to formulate the dosage of the exertion therapy for each patient. Using the prescription, each patient will also be advised on which physical activities they can safely do at home by themselves to promote fitness. During the therapy session, patients will be educated about the risk factors for CVD and they will be encouraged to eradicate the exposure or existence of the factors around them. Also, patients will be taught about healthy eating and importance of adhering to the medications and exercise therapy. BP and PR will be checked before and after each session to optimize safety of the patients. Also, each patient will be asked if they are facing challenges at home that are related to utilization of the therapy and exerting

at home; these will be recorded and where possible solutions will be devised. Thereafter, exercise therapy will be implemented and patients will do exactly what they were taught to do on the initial screening day and supervision will be offered throughout treatment sessions.

While participants in the Arm 1 of the trial receive both treatment modalities of CR (counselling/education and exercise therapy) and their cardiologists' prescribed cardiac medications, participants in the Arm 2 will receive the prescribed cardiac medications and education about their condition (nature of disease, risk factor modification, compliance to medications, nutritional needs); participants in Arm 2 (the control group) will come at baseline, and after 4, 8, 12 and 24 weeks for assessment and education. Figure 2 illustrates the circuit training program that will be followed during the therapy sessions. The exercise session will start with a warm up session and end with a cool down session; both sessions will be done in a group. The Arm 1 participants shall be asked to carry out two therapy sessions for each week at home, and attend a session each week at the hospital. This will assist in reducing the travel costs and avoid losses to follow up. Nevertheless, supervision at home is essential to ensure safety of the patients and efficacy of the treatment at home. Therefore, one guardian for each participant will be trained on how they will supervise the therapy sessions at home. A one-day training for the guardians will be given. All patients will be given the same home-therapy program; box stepping, walking and jogging for a predetermined FITT based on each participants' exertion capacity. The intervention will be delivered over a 12 weeks' period; participants will visit the hospital once a week and perform the rest of therapeutic tasks at home on two extra days per week for the 3 months. After the twelve-week period, all participants will be followed up for a period of twelve more weeks. All COVID-19 preventive measures namely; hand hygiene, social distance and surface/equipment disinfection will be observed. Therapists will use surgical masks during exercise therapy sessions, and patients will be asked to put on the masks before and after the exercise therapy session because they may not be able to breath while exerting.

**Table 1.** The reference benchmark for exercise prescription

|                                                                            | Frequency                   | Intensity                                                                             | Time                                                                                 | Type                                                                                                    |
|----------------------------------------------------------------------------|-----------------------------|---------------------------------------------------------------------------------------|--------------------------------------------------------------------------------------|---------------------------------------------------------------------------------------------------------|
| Cardiovascular Training
(exercises to enhance cardiovascular endurance) | 3 times a week for 12 weeks | 40-70% Heart Rate Reserve (HRR)
12-14 Rating of Perceived Exertion (RPE)           | 55 minutes (15 minutes warm up, 30 minutes conditioning phase, 10 minutes cool down) | Aerobics (treadmill, board stepping, cycling, point marching)                                           |
| Strength training
(Exercises to improve muscular strength)              | 2 times a week for 12 weeks | 30-70% 1 Repetition Maximum (1RM)
(30-40% 1RM: upper body, 50-60% 1RM: lower body) | 2-4 sets of 10-15 repetitions                                                        | Resistant exercises
(8-10 different muscle groups: weight lifting and pulleys, thera-band stretches) |

[figure not shown]

**Figure 2:** A circle showing the stages which will be followed during the delivery of exercise therapy, a component of CR intervention

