### ***Specific Objectives:***

1. To describe improvements in cardiovascular function at rest and on exercise among patients with a diagnosis of CHF
2. To describe the frequency of hospitalization among patients diagnosed with CHF enrolled into the cardiovascular rehabilitation program (CRP).
3. To describe the challenges that may be associated with establishment of a CRP at the QECH.

**Study design, population, sample size and sampling strategy:** This will be a prospective open label clinical trial of patients being discharged from the medical wards at QECH with a diagnosis of CHF. There will be two arms in the study with a total of 80 participants; Arm 1 will comprise of 40 patients with CHF who will receive cardiovascular rehabilitation as an intervention of interest, along with the usual cardiac medications that also include secondary prevention drugs, while 40 patients with CHF in arm 2 will be on cardiac medications that also include secondary prevention medications and education but not the exercise component of cardiac rehabilitation. Each participant will pick unlabelled sealed envelope with a paper that has a number that will determine to which group he or she will belong to. Participants will be followed up for 24 weeks. Participants in arm 1 will have regular cardiovascular exercise training once a week for 12 weeks and followed up without active exercise training for another 12 weeks. Arm 2 participants shall receive education component of cardiac rehabilitation at baseline and during the time points they will come for screening. Participants in both arms 1 and 2 will

continue to take cardiac medications as per their cardiologist's prescription throughout the study period.

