### 4.3 Study population

Patients with CHF, who come for follow up medical care at the QECH chest clinic at QECH, shall constitute the target population.

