#### **4.4 Sample size, sampling method and study period**

This study will enrol patients with CCF, who will come for medical check-up during the eight-week period of study participants' enrolment. According to the medical register book, there is a varying number of CCF patients who come for the clinic each week. For instance, out of a total of 53, 212 and 130 patients who came to receive cardiac or respiratory related medical care through this chest clinic in January, February and March, 19, 45 and 28 patients had CCF respectively. The clinic was temporarily shut down between April and September due to COVID-19 pandemic, and it recently resumed its services. However, out of 77 and 116 patients who came to this chest clinic in October and November after resumption of the clinic's services this year, 5 and 13 patients had CCF. This shows a drastic reduction in the number of cases coming for medical care; nevertheless, the numbers have reduced as a strategy to avoid congestion in the clinic and protect the patients from contracting or spreading the SARS-2 virus that causes COVID-19. It is expected that the number of patients coming for this clinic will remain low until Malawi is declared COVID-19 free or further measures have been put in place to protect patients at this clinic. Therefore, the following formula has been used to calculate the sample size with reference to a similar study conducted by

Awotidebe et al. (2016) in Nigeria and the trend of cardiac patients attending the chest clinic at QECH;

$$n = \frac{[(Z_{\alpha} + Z_{\beta}) \times 2(\sigma)^2]}{(\mu_1 - \mu_2)^2}$$

Where  $\mu_1$ =mean in group 1,  $\mu_2$ =mean in group 2,  $Z_{\alpha}=0.9$ ,  $Z_{\beta}=0.84$  (power),  $\sigma=1.2$

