The sample size for this study is based on detecting the effect size (the difference between the groups) of 0.6 at 80% power with a two-tailed significance level of 0.05. Using the formula above, a total sample size of 40 was obtained for each group. Owing the attrition of dropout rates of 5%, the sample size required is 80 (40 on each arm). To avoid issues of bias in participant selection, all patients will be selected from the chest clinic at the hospital. According to the chest clinic records, both sexes and different adult age groups (usually 45 years and above) are presented on each clinic day. Numbers 1 and 2 will be put on small pieces of paper, which will be placed in sealed and unmarked brown envelopes. Each participant will be asked to pick one envelop that will determine to which group she or he will belong to; this will assist in avoiding the selection bias. In addition, to ensure that the sample size is reached, discussions will be done with the head of the chest clinic to schedule more patients with CCF within the study participants' enrolment period. According to the available recommendations worldwide, 10 patients are allowed to exercise using a circuit training approach for an hour, and 3-4 therapists must be available to supervise the program to ensure safety. Because access to the Physiotherapy department at QECH to implement this pilot intervention is in the afternoon (13:00-12:00pm), and the number of patients enrolled into the active Arm is 40, the College of Medicine Physiotherapy gym will be used; and therapy session will be every Wednesday from 8:30 am to 12:30 pm. Nevertheless, the Physiotherapy department at QECH will be actively involved in the care delivery of these patients at College of Medicine Physiotherapy gym throughout the study, for capacity building and to ensure continuity of care after the implementation of this study. The participants shall be recruited over a period of two months.

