| ACTIVITY                                      | COMPLETION DATE   | RESPONSIBLE PERSON   | Key authority |
|------------------------------------------------------|--------------------------|-----------------------------|----------------------|
| Ethical approval                                     | September-October, 2020  | Investigators               | Investigators        |
| Site permission                                      | September-November, 2020 | Investigators               | Investigators        |
| Training and final discussions with all stakeholders | December, 2020           | Investigators               | Investigators        |
| Screening for enrollment                             | January-February, 2021   | Investigators               | Investigators        |
| Therapy implementation                               | February-March, 2021     | Investigator and therapists | Investigators        |
| Data management and analysis                         | April, 2021              | Investigators               | Investigators        |
| Report writing                                       | May-July 2021            | Investigators               | Investigators        |
| Dissemination of results                             | August-October, 2021     | Investigators               | Investigators        |

**Table 4:** Budget items for the study (1USD: 750MWK)

| ITEMS     | SPECIFICATION          | QUANTITY | COST PER ITEM                                          | TOTAL COST (MK) | TOTAL COST (\$) | JUSTIFICATION                                                                                                                                                                                     |
|-----------|------------------------|----------|--------------------------------------------------------|-----------------|-----------------|---------------------------------------------------------------------------------------------------------------------------------------------------------------------------------------------------|
| PERSONNEL | Cardiologist/Physician | 1        | MK20,000/session for 12 sessions                       | MK240,000       | \$320           | For medical enquiries, such as to do with medications. This will also be a focal person in all referrals into the study.                                                                          |

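### The protocol's own clinic counts do not support 80 patients in a fixed eight-week enrolment window, and Table 3 schedules the analysis before any participant can reach week 24

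*Protocol*

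**What the plan says.** **Target and window.** Section 4.4 concludes that "the sample size required is 80 (40 on each arm"). It draws everyone from the chest clinic and adds: "The participants shall be recruited over a period of two months". Section 4.5 turns this into a stop rule: "The referring of patients for screening and enrolment shall be terminated after the eight-week period". Neither section provides for an extension.

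**Expected supply.** Section 4.4 reports 19, 45 and 28 heart-failure patients at the clinic in January, February and March. After the COVID-19 closure, for October and November, it reports: "this year, 5 and 13 patients had CCF". It attributes the fall to a deliberate reduction in attendance and continues: "It is expected that the number of patients coming for this clinic will remain low until Malawi is declared COVID-19 free". The same sentence allows for recovery if further protective measures are introduced. To secure the sample size, the investigators will talk to the head of the clinic about booking more heart-failure patients during the enrolment period. No number is attached.

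**Source.** Section 4.3 defines the population as "Patients with CHF, who come for follow up medical care at the QECH chest clinic". The executive summary describes "patients being discharged from the medical wards at QECH with a diagnosis of CHF".

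**Calendar.** Table 3 (section 10.0) puts screening in January-February 2021, therapy in "February-March, 2021" and data analysis in April 2021. Section 4.5 fixes a 12-week programme followed by 12 more weeks of follow-up, and section 6.0 plans comparisons at 3 and 6 months.

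**The concern.** Enrolment ends when time runs out, whatever number has been reached, and the only supply figures in the protocol fall short of the target. The counts cover every heart-failure patient seen, before residence, consent, ability to exercise and the high-risk exclusion are applied. They may also include repeat visits. The true supply of eligible, distinct patients is therefore lower by an amount the protocol does not give.

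If the window is kept and the counts are a fair guide, the trial closes with fewer than 80 patients, and the precision claimed in section 4.4 does not describe the trial that will be run.

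The calendar is a second problem. The executive summary expects benefits to persist at 24 weeks. On the dates in Table 3, the analysis would take place with no 24-week data from anyone.

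**Working it through.** **1. The target.** The 80 is taken here as the stated target. It is not reproduced from its own inputs. The printed formula gives (0.9 + 0.84) × 2 × 1.2² / 0.6² = 13.9, so 14 per arm. Squaring the Z sum gives 24.2, so 25. With Z = 1.96 for two-sided 5% it gives 62.7, so 63. Reading 0.6 as a standardised effect gives 44. None is 40. That is a separate issue, and nothing below depends on it.

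**2. Supply over two months (counts from section 4.4).**

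| Months | Heart-failure patients | Share of 80 |
|---|---|---|
| October + November | 5 + 13 = 18 | 22.5% |
| January + February | 19 + 45 = 64 | 80% |
| February + March | 45 + 28 = 73 | 91% |

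With every attender enrolled, 80 would need 80/18 = 4.4 times the October-November level, or 80/73 = 1.1 times the February-March level.

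**3. Scaled to eight weeks (56 days).** October-November: 18/61 × 56 = 16.5. February-March: 73/60 × 56 = 68.1, assuming the counts are from 2020. At the October-November rate, 80 patients take 80/(18/8.71 weeks) = 38.7 weeks. The protocol does not say whether the clinic ran throughout October, so this lower rate is approximate.

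**4. Eligibility and consent.** The protocol gives no rate. Assuming 50% to 90% of attenders are eligible and consent, two months yield 9 to 16 patients at the latest rate (18 × 0.5 to 18 × 0.9) and 37 to 66 at the best rate (73 × 0.5 to 73 × 0.9). To enrol 80, between 80/0.9 = 89 and 80/0.5 = 160 attenders would be needed.

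**5. What the smaller numbers can detect.** These are for a two-sample t-test, two-sided 5%, 80% power, equal arms and no dropout. The normal approximation is d = (1.96 + 0.84) × √(2/n per arm). The t-based values are slightly larger. The protocol's difference of 0.6 with SD 1.2 is 0.5 SD.

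| Patients | Per arm | d, approximation | d, t-test | Power for 0.5 SD |
|---|---|---|---|---|
| 18 | 9 | 1.32 | 1.41 | 17% |
| 68 | 34 | 0.68 | 0.69 | 53% |
| 80 (planned) | 40 | 0.63 | 0.63 | 60% |

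**6. Calendar.** February and March 2021 together are 59 days, or 8.4 weeks, for a 12-week programme. A patient enrolled on 1 January 2021 reaches week 24 on 18 June 2021, and one enrolled on 28 February reaches it on 15 August 2021. Both dates fall after April.

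**The case against.** **Past attendance is not a ceiling.** A reader might infer that 80 cannot be reached. The protocol does not show that. Attendance after reopening was held down on purpose, it rose from 5 to 13 in a month, and section 4.4 contains a measure aimed at this very problem. This stands.

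**Booking more heart-failure patients need not conflict with decongestion.** October and November had 77 + 116 = 193 attendances, 18 of them (9%) for heart failure. Giving more existing slots to these patients adds no crowding. But 80 would be 41% of those slots, against 92/395 = 23% in January-March. At 23%, 193 attendances yield about 45 patients. The measure is possible but demanding, and it is unquantified.

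**The power shortfall is not all due to accrual.** At the planned 80, power for 0.5 SD is already only 60%. At the best rate, slow accrual costs about 7 points (60% to 53%), so the best case does not void the sample-size statement. This also stands.

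**The two sources may be compatible.** A reader might see ward discharges and clinic attenders as contradictory. Section 4.31 requires a diagnosis at hospital discharge, and section 4.4 recruits at the clinic. Diagnosed at discharge and recruited at follow-up is a coherent reading, so only the executive summary's wording needs aligning.

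**This is a pilot, and Table 3 is administrative.** A fixed window is acceptable in a pilot, and slow accrual would itself be informative. But section 4.4 makes a formal 80% power claim, so the size must match the window. The methods sections do fix 24 weeks of follow-up, and the amendment request of 4 June 2021 already postdates the April analysis slot. The investigators may never have meant to analyse then, but the table still contradicts the design.

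**Conclusion.** The concern holds in a limited form. The stated size is not supported by the protocol's own counts in the stated window: 18 to 73 heart-failure attenders in two months, before exclusions and refusals, against 80. The one remedy has no number and no fallback. The consequence ranges from severe (about 1.4 SD detectable at the October-November level) to modest (0.69 SD against 0.63 SD at the February-March level). Where the trial would fall depends on attendance, repeat visits, eligibility and consent, none of which the protocol forecasts. It does not follow that 80 is unattainable.

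The Table 3 conflict needs no accrual assumption. On its dates, the programme does not fit and no participant has a 24-week outcome at analysis.

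**What to change.** 1. **Sections 4.4 and 4.5.** State the number of distinct, eligible patients realistically expected in eight weeks, including any agreed increase in bookings, and print the detectable difference at that number. This costs a review of the clinic register and some wording.
2. **If the sponsor keeps 80 as the target,** replace the eight-week stop with enrolment until 80 are allocated or a stated latest date. This is not just a wording change. Table 4 budgets the four physiotherapists for 12 sessions. At the October-November rate, weekly sessions would run for about 39 + 12 = 51 weeks, roughly four times that line. The added sessions and staff time must be acknowledged and funded.
3. **Table 3.** Redraw it so that therapy spans the 12-week programme for the last patient enrolled and analysis follows the last 24-week visit. On the stated enrolment dates, that visit is in mid-August 2021, so reporting and dissemination move later too.
4. **Executive summary.** Align the recruitment source with the chest-clinic source in sections 4.3 and 4.4. This is wording only.

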### **PRESCRIPTION (40-60% HRRMAX)**

Results in use: HR..... METS achieved:..... RPE:

Prescribed zone: %HRR..... METS max: RPE:

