### **HOME PROGRAM**

| EXERCISE          | DOSAGE | PHYSICAL ACTIVITIES ENCOURAGED? |
|-------------------|--------|---------------------------------|
| STAIR STEPPING    |        |                                 |
| STRENGTH TRAINING |        |                                 |
| WALKING           |        |                                 |

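### The Arm 1 exercise prescription conflicts within the current protocol on three points: the test that sets the target zone, the aerobic intensity ceiling, and whether strength work is done at home

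*Protocol*

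**What the plan says.** All of the following is current protocol text. The form referred to is the step-test and prescription form in the appendices.

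**Test.** Section 4.5 says the 6-minute walk test will help therapists set each patient's target exertion zone. Section 4.7 assigns prescription to the Chester step test (Appendix 9) and uses the walk test for exertion tolerance. The form likewise places the prescription block after a stage-by-stage step-test record.

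**Intensity.** Section 4.5 makes Table 1 the source of the dose: "Table 1 describes the parameters which will be used to formulate the dosage of the exertion therapy for each patient". For aerobic work Table 1 gives "40-70% Heart Rate Reserve (HRR)" together with "12-14 Rating of Perceived Exertion (RPE)". The form's prescription block is headed "PRESCRIPTION (40-60% HRRMAX)", while the line below it asks for a zone in %HRR. Near the top, the form also has a field for 70% HRR whose purpose is not stated.

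**Strength work.** Table 1 sets strength training at "2 times a week for 12 weeks". On the split between hospital and home, section 4.5 says that "participants will visit the hospital once a week and perform the rest of therapeutic tasks at home on two extra days per week". On home content it says: "All patients will be given the same home-therapy program; box stepping, walking and jogging". The home programme on the form has rows for stair stepping, "STRENGTH TRAINING" and walking. Jogging is not among them.

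**The concern.** The participants have heart failure, and two of their three weekly sessions take place at home under a guardian who has had one day of training. Section 4.6 relies on that guardian supervising a prescribed home programme so that exertion is safe. This needs one programme, one heart-rate ceiling and one test from which the ceiling is derived. Section 5.0 plans standard operating procedures so that all assistants work identically. Someone drafting them from section 4.5 and Table 1 would arrive at a different home programme and a different ceiling from someone drafting them from the form. The pilot is also meant to inform roll-out at the hospital and elsewhere (section 2.0), so the intended regimen should be stated consistently.

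**Working it through.** **1. Test.** Section 4.5: the walk test informs the target zone. Section 4.7: the Chester step test is for prescription and the walk test for tolerance. The amendment request gives the same division as section 4.7, so the intent is clear. The 4.5 sentence was not brought into line.

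**2. Intensity.** Inputs: 40-70% HRR (Table 1) and 40-60% (form).

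- Difference in ceilings: 70 - 60 = 10 percentage points of HRR.
- Share of Table 1's band above the form's ceiling: 10 / (70 - 40) = 33%.
- In beats/min the difference is 0.10 × HRR. The protocol gives no reserve values. Over an assumed range of 40 to 100 beats/min it is 0.10 × 40 = 4 to 0.10 × 100 = 10 beats/min.
- A prescription of 65% HRR is allowed by Table 1 and falls outside the form's range. Any prescription from 40% to 60% satisfies both.

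**3. Strength sessions over 12 weeks.** Inputs: 2 strength sessions a week (Table 1); 1 hospital and 2 home sessions a week (section 4.5). Figure 2, the circuit, is not shown, so I assume that every hospital session includes strength work.

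| Reading | Hospital | Home | Total | Against Table 1 |
|---|---|---|---|---|
| Table 1 | – | – | 2 × 12 = 24 | – |
| 4.5 home list taken as complete | 1 × 12 = 12 | 0 | 12 | 12 short (50%) |
| Form's home list | 12 | 0 to 2 × 12 = 24 | 12 to 36 | 24 attainable |

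The first reading gives a maximum: if some hospital sessions omit strength work, fewer than 12 are delivered.

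As a check, aerobic frequency does reconcile. Table 1 asks for 3 × 12 = 36 sessions, and 12 hospital plus 24 home sessions make 36. The frequency mismatch is therefore confined to strength work.

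**The case against.** The strongest reply is that these are drafting slips with little consequence.

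- **Nested ranges.** Table 1 is captioned as a benchmark, doses are individualised, and anything within 40-60% complies with 40-70%. The perceived-exertion limit applies as well. HRRMAX looks like a slip, since the next line reads %HRR. This stands as far as it goes, but it does not say whether 65% is permitted, and section 4.5 makes Table 1 the dosing rule. The 70% HRR field may be a test-stopping limit. If so, the two prescription ceilings still differ.
- **Strength work.** Section 4.5 also sends the remaining tasks home, which could include strength work, and the form provides a row for it. This is correct, and it makes the shortfall conditional. It also means that section 4.5 can be read in two ways.
- **Test.** The intent is settled and only one sentence is out of date. I agree, but that sentence is in the section that governs the intervention.
- **Jogging.** It could be entered in the form's physical-activities columns, so its absence as a row is a minor matter.

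A reader might infer that the pilot could not report what dose was prescribed. The documents do not support this. Doses are set per patient, and the form has fields for each patient's zone, strength loads and home dosage.

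**Conclusion.** The conflict is real and should be corrected, mainly because it concerns exertion limits and home supervision in heart-failure patients. Its three parts differ in weight:

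- The test is one unrevised sentence.
- The ceilings differ by 10 percentage points of HRR, or 4 to 10 beats/min under the assumed reserve of 40 to 100 beats/min.
- The strength shortfall is at least 12 of 24 sessions if the 4.5 home list is followed as complete. It can be zero if the form is followed.

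It would be tempting to conclude that Arm 1 will receive half the planned strength work. The documents do not establish that: the figure depends on which text is followed and on the assumption about hospital sessions. Nor do they support any effect on sample size, alpha or power.

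**What to change.** 1. **Section 4.5, test.** Reword the sentence along these lines: *Exercise tolerance will be measured with the 6-minute walk test; each patient's exercise zone will be prescribed from the Chester step test (Appendix 9).*
2. **Intensity.** Use 40-60% HRR in Table 1 and on the form, since it satisfies both texts, unless the clinical lead justifies 70%. Replace HRRMAX with HRR. State what the form's 70% HRR field is for, for example a limit at which the test stops.
3. **Home programme.** List the same exercises in section 4.5 and on the form, with jogging kept or removed in both. Then choose one of two options:
   - put strength work in one of the two home sessions, using items patients can have at home, which gives (1 + 1) × 12 = 24 sessions and meets Table 1; or
   - set strength frequency in Table 1 to once a week, which gives 12 sessions, all deliverable at the hospital.

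**Cost.** Items 1 and 2 are wording only. Item 3 may cost more. Table 1's strength work relies on weights, pulleys and elastic bands, and the only equipment the budget assigns to homes is 15 stepping boxes, for an arm of 40 patients. Home strength work may therefore need some equipment and added guardian instruction. The once-weekly option avoids this but lowers the stated dose. The choice between them is clinical. Neither option adds visits or patients.
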